## Abstract

**Introduction:**

A high BMI during and after pregnancy is linked to poor pregnancy outcomes and contributes to long-term maternal obesity, hypertension, and diabetes. Evidence of feasible, effective postnatal interventions is lacking. This randomised controlled trial will assess the feasibility of conducting a future definitive trial to determine effectiveness and cost-effectiveness of lifestyle information and access to Slimming World® (Alfreton, UK) groups for 12 weeks commencing from 8 to 16 weeks postnatally, in relation to supporting longer-term postnatal weight management in women in an ethnically diverse inner city population.

**Methods/analysis:**

Women will be recruited from one maternity unit in London. To be eligible, women will be overweight (BMI 25–29.9 kg/m^2^) or obese (BMI ≥ 30 kg/m^2^) as identified at their first antenatal contact, or have a normal BMI (18.5–24.9 kg/m^2^) at booking but gain excessive gestational weight as assessed at 36 weeks gestation. Women will be aged 18 and over, can speak and read English, expecting a single baby, and will not have accessed weight management groups in this pregnancy. Women will be randomly allocated to standard care plus lifestyle information and access to Slimming World® (Alfreton, UK) groups or standard care only. A sample of 130 women is required.

Feasibility trial objectives reflect those considered most important inform a decision about undertaking a definitive future trial. These include estimation of impact of lifestyle information and postnatal access to Slimming World® (Alfreton, UK) on maternal weight change between antenatal booking weight and weight at 12 months postbirth, recruitment rate and time to recruitment, retention rate, influence of lifestyle information and Slimming World® (Alfreton, UK) groups on weight management, diet, physical activity, breastfeeding, smoking cessation, alcohol intake, physical and mental health, infant health, and health-related quality of life 6 and 12 months postnatally. An embedded process evaluation will assess acceptability of study processes and procedures to women.

**Ethics/dissemination:**

London–Camberwell St Giles Research Ethics Committee, reference: 16/LO/1422. Outcomes will be disseminated in peer-reviewed journals and presentations at national and international conferences.

**Trial registration:**

Trial registration number: ISRCTN 39186148. Protocol version number: v7, 13 August 17. Trial sponsor: King’s College London.

## Strengths and limitations of this study

Postnatal interventions may be more effective than antenatal interventions at supporting weight management among women with higher BMIs, but evidence is needed.This feasibility trial will assess if women with high BMIs at pregnancy commencement or have normal BMIs but gain excessive gestational weight would be prepared to be randomised to standard care plus Slimming World® (Alfreton, UK) groups offered from 8 to 16 weeks postnatally, or to standard care only.Women will only be recruited from one study site; however, the site provides maternity care to a population with wide diversity. The intervention is available UK-wide.Blinding of study participants and assessors is not possible.

## Introduction

At around 6 to 8 weeks postnatally, two thirds of women weigh more than their pre-pregnancy weight [1], with evidence that women who commence subsequent pregnancies overweight or obese have higher risk of adverse outcomes for themselves and/or for their infants. Furthermore, a high BMI before, during, and after pregnancy is linked to poor maternal health behaviours including smoking, lack of regular exercise, and not breastfeeding [2–4]. Maintaining a high BMI postnatally is an important predictor of maternal future weight gain and obesity, hypertension, diabetes, and degenerative joint disease [5–7], with infants of obese women at greater risk of higher BMI and blood pressure in childhood and young adulthood [4]. In the absence of evidence to support the benefit of pregnancy weight management interventions and positive lifestyle behaviours, postnatal interventions are viewed as increasingly important [8, 9] in terms of enhancing life-course health and preventing adverse outcomes in subsequent pregnancies, but knowledge of how best to support and treat overweight or obese individuals, including postnatal women, remains a challenge [10, 11]. The timing of commencement, recruitment approaches, and content of postnatal interventions are unclear [5], including how best to ensure that socio-economic influences which may impact on maternal health and lifestyle behaviours are considered. This is important, as a significantly greater proportion of women from areas of high social deprivation in the UK have weight management problems [12], findings supported with work from the USA where excessive pregnancy weight gain and failure to lose weight were found to be highly prevalent among young, low income, ethnic minority women in one large cohort study [13].

Although around half of all UK women of reproductive age are overweight or obese [14], UK public health guidance does not recommend dieting and weight loss during pregnancy due to concerns about impact on infant outcomes [15] despite lack of evidence [16], and there is no current UK guidance on recommended pregnancy weight gain. Pregnancy-only interventions have measured impact on adverse outcomes including gestational diabetes, large for gestational age infants and caesarean births [17–20]. UPBEAT, a UK-based multicentre trial of a behavioural intervention based on changing diet to foods with a lower glycaemic index and increasing physical activity, aimed to reduce risk of gestational diabetes and large for gestational age infants [21]; 1555 women with a mean BMI of 36.3 kg/m^2^ (SD 4.8) were recruited. No differences were found in incidence of outcomes of interest. Gestational diabetes was reported in 172 (26%) women in standard care compared with 160 (25%) in the intervention group (risk ratio 0.96, 95% CI 0.79–1.16; *p* = 0.68). Sixty-one (8%) of 751 babies in the standard care group were large for gestational age compared with 71 (9%) of 761 in the intervention group (1.15, 0.83–1.59; *p* = 0.40).

Recent systematic reviews of postnatal interventions have highlighted the potential importance of these, but reported gaps in evidence of ‘what works’ and the low quality of evidence. A Cochrane review of diet and/or exercise for postnatal weight reduction [22] in which 12 trials contributed data on 910 women found women who exercised did not lose significantly more weight than women in usual care groups (two trials, *n* = 53, mean difference − 0.10 kg, 95% CI − 1.90 to 1.71), but women who took part in a diet (one trial, *n* = 45, mean difference − 1.70 kg, 95% CI − 2.08 to − 0.132) or diet plus exercise programme (seven trials, *n* = 573, mean difference − 1.93 kg, 95% CI − 2.96 to − 0.89) lost significantly more weight than women in usual care groups. Trials included women who were obese, overweight, or gained excessive gestational weight, with recruitment from 3 weeks to 24 months postpartum. Intervention duration ranged from 10 to 24 weeks, with content often delivered as a ‘package’. Only one trial was from the UK. Despite considerable study heterogeneity, the authors suggested diet and exercise together rather than diet alone could help women to lose weight postnatally because the former could improve women’s cardiovascular fitness level and preserve fat-free mass.

van der Pligt and colleagues completed a systematic review of interventions to reduce postpartum weight retention across all BMI categories [5]. Studies were included if postpartum weight was a primary outcome, and diet and/or exercise and/or weight monitoring were intervention components. Interventions commenced from 11 days to 9 months postpartum and included counselling, individualised physical activity plans, healthy eating groups, and clinic visits. Of 11 studies included, 10 were RCTs, none from the UK. Seven reported a decrease in postpartum weight retention, six of which included diet and physical activity delivered by different health professionals. No study considered cost-effectiveness, with wide heterogeneity in intervention implementation. Nevertheless, findings suggested that postnatal weight loss was achievable, although evidence of optimal setting, implementation, intervention duration, and recruitment approach was unclear.

The potential for postnatal interventions to impact on other maternal health behaviours was considered in a review by Hoedjes et al. [23] which also reported poor-quality evidence. Eight of 17 included studies assessed effects on weight loss, and 9 on smoking cessation and relapse prevention. Of the weight loss studies, five reported significant effects of combined diet and exercise. Two of the four studies which assessed smoking relapse prevention found no evidence of effect. Four studies included interventions for smoking prevention and prevention of relapse. Although authors recommended that existing postpartum lifestyle interventions could support weight loss and smoking cessation or prevent smoking relapse, caution is needed. There was wide variability in study methods, and details of study selection, data extraction processes, and assessment of study quality were not provided.

The potential for the postnatal period to be a more appropriate time to consider support for weight management and positive lifestyle behaviours is clear, yet high-quality evidence of effective interventions is lacking. Based on evidence from general population studies that commercial organisations may be more effective at supporting weight management than healthcare providers [24], this trial is being undertaken to assess the feasibility of conducting a future definitive RCT to determine effectiveness and cost-effectiveness of lifestyle information and access to Slimming World® (Alfreton, UK) groups for a 12-week period, from 8 to 16 weeks postnatally, on long-term postnatal weight management and positive lifestyle behaviour among women from an ethnically diverse inner city population.

## Objectives

The following are the specific trial feasibility and trial process objectives to inform if a future definitive trial could be undertaken. Findings will inform if postnatal women would be prepared to enter a study of weight management, when would be an optimal time to intervene, content of a pragmatic and accessible intervention, if an intervention could impact on other health areas, and outcomes likely to be of most importance in a future trial.

### Trial feasibility objectives

The trial feasibility objectives are as follows:
To assess recruitment and retention ratesTo estimate the effect size for a likely primary study outcome in a future definitive trial, namely difference between study groups in weight change from booking to 12 months postbirth, expressed as percentage of weight change or weight loss in kilogrammesTo estimate impact of lifestyle information and access to Slimming World® (Alfreton, UK) groups on maternal weight change from first antenatal visit to 12 months postnatallyTo explore influence of lifestyle information and access to Slimming World® (Alfreton, UK) groups including weight management, diet, physical activity, breastfeeding, smoking cessation, alcohol intake, physical and mental health, infant health, sleep patterns, body image, self-esteem, and health-related quality of life at 6 and 12 months postnatallyTo assess resource impacts across different agencies likely to be of relevance and identify data appropriate for economic evaluation in a definitive RCTTo decide if criteria to inform progression to a definitive RCT have been met

### Trial process evaluation objectives

The trial process evaluation objectives are as follows:
To assess acceptability of trial procedures and interventionTo assess variation in Slimming World® (Alfreton, UK) groups attended by womenTo assess sources of weight management support accessed by women (in particular assess risk of contamination) (Table 1)

**Table 1 Tab1:** Study objectives, outcomes, criteria for success, and method of analysis

Objectives	Feasibility outcomes (trial)	Criteria for success	Method of analysis
Maternal weight change (proposed primary endpoint for future definitive RCT)	Difference in percentage of maternal weight change between trial groups from antenatal booking to 12 months postnatally	Percentage of weight change/weight loss in kilogrammes	Estimated differences/95% CI calculated (significance at 5%) Pre-planned sub-group analysis by BMI category
Recruitment and retention	Uptake/time to recruit 190 women from BMI categories of interest	Complete recruitment within 6 months	Descriptive
	Loss to follow-up under 30% at 12 months	Retain 130 women to 12 months	Descriptive
Explore influence of lifestyle information and Slimming World on lifestyle/health behaviours	Dietary intake, EPDS score, breastfeeding uptake and duration, sleep patterns, smoking, alcohol consumption, self-esteem, infant health, body image	High completion of all included measures at each follow-up point	*N* (%) for binary and categorical variables and mean (SD), or medians/geometric means for continuous variables
Assess feasibility of collecting resource utilisation and cost data	Completion of EQ-5D-5L, Adult Service Use Schedule, relevant data from women’s maternity records	High completion of all included measures at each follow-up point	Multivariate/sensitivity analysis
Objectives	Outcomes (process)	Criteria for success	Method of analysis
Acceptability of trial process procedures	Reasons for taking part/dropping out, expectations, understanding of study aims, attendance at follow-up appointments, acceptability of surveys	Processes and procedures acceptable, high completion of follow-up measures	Framework method, descriptive
Acceptability of intervention	Women commence and complete Slimming World sessions offered	Depth of understanding of barriers and facilitators to uptake and retention at sessions, so this can be maximised in a future trial	Framework method, descriptive
Variation in Slimming World groups attended by women by date/time of day	Range of variation in Slimming World groups attended	Availability of data from Slimming World	Descriptive
Sources of weight management support control group accessed/additional support intervention women accessed	Extent and type of weight management support used by control women, additional support used by intervention women	Risk of contamination re access to commercial weight management support by control group	Descriptive

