### Sample size calculation, selection, and loss to follow-up

A sample size of 190 women will allow a 30% loss to follow-up to ensure we achieve our required sample size of 130 women. This study is designed firstly to establish the rates at which women could be recruited and retained in a future definitive RCT and estimate critical parameters with necessary precision to inform sample size requirements. In particular, we require estimates of the standard deviation, and design effect for the primary endpoint, allowing for clustering by intervention group. One hundred thirty women will allow estimates of the required sample size for any given clinically important difference to within 30% of the true value.

Based on published data [17, 42] the mean (SD) percentage weight change following a Slimming World® (Alfreton, UK) programme of 12 weekly groups is − 5.5% (3.3). Assuming these numbers are typical, 65 women in each group (130 in all) would be required to detect a difference of 2% between active and control groups with 90% power. Of around 6600 women who give birth at the reference maternity unit over 12 months in 2017, 40% were overweight, 15% of whom were obese. Data on women with excessive GWG are not routinely collated. Potentially, 55 women booking each week would meet obese/overweight inclusion criteria. Recruiting 7–8 women each week over an 8-month (32 week) period would be sufficient to achieve the desired sample size to meet the aims of this feasibility study.

Compliance issues are an important consideration. Loss to follow-up among postnatal women can range from 30 to 40% [43, 44]. Experience of research in similar populations has shown that planned initiatives including flexible follow-up appointments, travel expenses, vouchers for returning questionnaires, and sending of reminders can reduce loss to follow-up. Follow-up appointments will be offered at weekends and week days, with the option to complete questionnaires at these appointments.

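### The 6-month success criterion for recruiting 190 women conflicts with the 8-month (32-week) recruitment period, and the stated 7–8 women a week does not match that period

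*Protocol article*

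**What the plan says.** In Table 1 of the protocol article, the first recruitment and retention row gives the outcome as "Uptake/time to recruit 190 women from BMI categories of interest" and the criterion for success as "Complete recruitment within 6 months". The analysis is descriptive.

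The section on sample size calculation, selection and loss to follow-up sets the target: "A sample size of 190 women will allow a 30% loss to follow-up to ensure we achieve our required sample size of 130 women". It then states the pace: "Recruiting 7–8 women each week over an 8-month (32 week) period would be sufficient to achieve the desired sample size".

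The trial feasibility objectives include deciding whether the criteria that inform progression to a definitive trial have been met. The article gives no other set of criteria than the success column of Table 1.

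**The concern.** Both places describe recruitment of the same women to the same trial, yet one allows 6 months and the other 8. The weekly rate printed beside the 8-month period also seems to belong to a period of about 6 months.

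This matters because the sample size section puts recruitment and retention rates first among the things the study is designed to establish. In Table 1 only recruitment and retention have numerical success criteria; the remaining rows rely on phrases such as high completion. If one of the two numerical criteria has two possible thresholds, the same observed recruitment time can be reported as success or as failure. The document gives no rule for choosing between them once the result is known.

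**Working it through.** **Inputs**
- Target: 190 women recruited (Table 1 and the sample size section).
- Success criterion: 6 months (Table 1).
- Planned period: 8 months, given as 32 weeks (sample size section).
- Planned rate: 7–8 women a week (sample size section).
- Assumption: Table 1 does not express 6 months in weeks. I use 24 weeks (the document's own 4 weeks per month) and 26 weeks (half a calendar year).

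**Step 1. The target itself reproduces.** 130 / (1 − 0.30) = 185.7, so 186 women, and 190 × 0.70 = 133. The figure of 190 is sound, so the mismatch lies in the timing.

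**Step 2. Yield of the stated rate, N = rate × weeks.**

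| Period | At 7 a week | At 8 a week | Against 190 |
|---|---|---|---|
| 32 weeks | 224 | 256 | 34–66 too many (18–35% above) |
| 26 weeks | 182 | 208 | brackets 190 |
| 24 weeks | 168 | 192 | reaches 190 only near the top rate |

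If the desired sample size is read as 130, the 32-week yield is 72–97% above it (224/130 = 1.72; 256/130 = 1.97). The stated rate and period together give neither 190 nor 130.

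**Step 3. Time to reach 190 at the stated rate, weeks = 190 / rate.** 190/7 = 27.1 weeks and 190/8 = 23.8 weeks. The stated rate therefore implies about 24–27 weeks, not 32.

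**Step 4. Rate needed for each period, rate = 190 / weeks.**
- 32 weeks: 190/32 = 5.9 a week.
- 26 weeks: 190/26 = 7.3 a week.
- 24 weeks: 190/24 = 7.9 a week.

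**Step 5. Position at 6 months if recruitment just fills the 32-week window.** The rate is 190/32 = 5.94 a week.
- At 24 weeks: 5.94 × 24 = 142.5, about 143 women, or 75% of 190.
- At 26 weeks: 5.94 × 26 = 154 women, or 81% of 190.

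The 75% figure uses one month length throughout (6/8 = 0.75). The 81% figure combines a 4-week month for the 8-month period with a calendar half-year for the 6 months, so it is the milder end of the range.

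**Step 6. Outcome under each passage.**

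| Recruitment of 190 ends | Table 1 | Sample size section |
|---|---|---|
| Within 6 months | success | ahead of schedule |
| After 6 and up to 8 months | failure | on schedule |
| After 8 months | failure | late |

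The middle row is where the two passages disagree.

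**The case against.** The best defence is that the two statements serve different purposes. The sample size section says only that the rate would be sufficient, and 224–256 does exceed 190, so the sentence is literally true. A longer operational window can sit alongside a stricter benchmark. The recruitment section even suggests a reason for slack: women with a normal booking BMI are first sought by advertising, with an opt-out letter as fallback if they do not respond within 3 months. This is a fair possibility, but the document never makes the link, never calls 6 months a stricter target, and does not explain the surplus of 34–66 women.

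A reader might also infer that a trial recruiting to plan would fail its own progression test. The documents do not support that. The only rate they plan is 7–8 a week, and on a 26-week reading this meets the 6-month criterion at 7.3 a week or more and misses it by about one week at 7 (27.1 against 26 weeks). On a 24-week reading most of the range misses, but 8 a week still meets it. The 5.9 a week in the working is derived from 190 and 32 weeks; the protocol does not state it as a plan.

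Nor does the article state a binding stop/go rule. Table 1 speaks of success, and the objectives speak of criteria that inform progression. Treating the Table 1 column as those criteria is a reasonable inference, since no others are given, but it remains an inference.

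Finally, the mismatch leaves randomisation, the effect estimate, the targets of 190 and 130, and the retention criterion untouched. That limits its reach but does not remove the conflict between the two periods.

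**Conclusion.** The point holds as an unreconciled conflict in a stated decision threshold: 6 months in Table 1 against 8 months (32 weeks) in the sample size section for the same 190 women. The printed rate of 7–8 a week fits about 24–27 weeks and overshoots 190 by 18–35% over 32 weeks. The required rate is 5.9 a week on one reading and 7.3–7.9 on the other, and recruitment that just fills the longer window stands at 75–81% of target at 6 months.

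These sizes assume steady accrual and 6 months taken as 24 or 26 weeks. The conflict itself depends on neither assumption. It does not follow that the planned weekly rate leads to failure; what follows is that recruitment ending between 6 and 8 months has no single agreed interpretation.

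**What to change.** Before recruitment is judged, state one window in weeks and one matching weekly rate, and use both in Table 1 and in the sample size section. Two consistent versions are:

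- 190 women in 26 weeks, needing about 7.3 a week or more. The lower end of the present range, 7 a week, gives 182 and would have to be raised.
- 190 women in 32 weeks, needing about 6 a week (6 × 32 = 192), with Table 1 changed to 8 months (32 weeks).

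If 6 months is meant as a stricter benchmark inside a longer operational window, say so, give it in weeks, and name it as the criterion that informs progression.

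The cost is one table cell and one sentence, with notice to the Trial Steering Committee. No change to the design, sample size or analysis is needed.

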## Methods and analysis

This protocol paper has been written following the SPIRIT and TIDieR guidance [25, 26].

